### Randomization and statistics

Randomization is performed as a block randomization by the statistician. Patients are assigned randomly to one of the therapy arms by equal possibility for randomization for both arms.

According to a previous trial published by Niewald et al. (40) and an actual statistical calculation before beginning this study 120 patients are required in each arm and have to be evaluated over 48 weeks (inclusive a drop-out rate of 10% of the patients) in order to detect a difference of 15% in VAS and Calcaneodynia-Score with a power of 80% (error probability of 5%).

Statistics (primary and secondary endpoints) are performed using the MEDLOG software package (Fa. Parox, Münster) after observing the patients for 12 and 48 weeks and are controlled by the statistician.

### Primary endpoints (measured at 12 and 48 weeks after therapy)

SF-12 sum score [47,48]Calcaneodynia sum score [2,49]VAS self-assessment-score

The endpoints will be measured 12 and 48 weeks after radiotherapy, the results will be compared.

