**Methods:**

After approving a written informed consent the patients are randomized by a statistician into one of the trial arms. After radiotherapy, the patients are seen after six weeks, after twelve weeks and then every twelve weeks up to 48 weeks. Additionally, they receive a questionnaire every six weeks after the follow-up examinations up to 48 weeks. The effect is measured using the visual analogue scale of pain (VAS), the calcaneodynia score according to Rowe and the SF-12 score. The primary endpoint is the pain relief three months after therapy. Patients of both therapy arms with an insufficient result are offered a second radiotherapy series applying the standard dose (equally in both arms).

This trial protocol has been approved by the expert panel of the DEGRO as well as by the Ethics committee of the Saarland Physicians’ chamber.

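### The protocol article gives three incompatible versions of the primary endpoint, and no reading with more than one primary comparison is shown to keep both the stated 5% error and the 80% power

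*Protocol article*

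**What the plan says.** Three places in the protocol article bear on what decides the trial.

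- **Abstract, Methods:** "The primary endpoint is the pain relief three months after therapy". This is one endpoint at one time. No instrument is named for pain relief, although the sentence before it lists VAS, the calcaneodynia score and SF-12 as measures of effect.
- **Section headed "Primary endpoints (measured at 12 and 48 weeks after therapy":** the list reads "SF-12 sum score [47,48]Calcaneodynia sum score [2,49]VAS self-assessment-score". The only rule for using them is "The endpoints will be measured 12 and 48 weeks after radiotherapy, the results will be compared".
- **Randomization and statistics:** 120 patients per arm, including 10% drop-out, are required "in order to detect a difference of 15% in VAS and Calcaneodynia-Score", at 80% power and one 5% error probability. SF-12 is not named there. Analyses of primary and secondary endpoints are done "after observing the patients for 12 and 48 weeks and are controlled by the statistician".

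The Secondary endpoints section is separate. It lists the SF-12 and Calcaneodynia single scores and the event-free interval. The section Therapy protocol adds interim analyses after 120 and 180 enrolments, with randomization to stop if the groups differ significantly. It does not say on which endpoint.

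**The concern.** A protocol has to say which comparison decides the trial. Here a reader finds one comparison in the abstract, six in the endpoint section and two scores in the sample size. Depending on which is followed, the same data could be reported as positive or negative.

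The single 5% and the single 80% are also tied to no defined comparison. If several comparisons can each carry the trial, 5% is not the overall error rate. If several must succeed together, 80% at each does not give 80% overall. SF-12 is called primary without appearing in the power statement. The same gap reaches the interim stopping criterion, because a significant difference is not attached to any endpoint.

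**Working it through.** **Inputs from the document.** Three scores and two times (endpoint section); error 5%, power 80%, 120 per arm including 10% drop-out (Randomization and statistics). **Assumed, because the document does not give them:** correlations between test statistics, two-sided testing, a comparison of means, and 80% as the power for each score.

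**1. The plan's own figure.** Evaluable per arm: 120 × 0.9 = 108. The 120 cannot be reproduced, since there is no standard deviation or response rate, no sidedness, and no statement whether the 15% is absolute or relative. Solving backwards for a two-sided comparison of means: d = (1.960 + 0.842) × √(2/108) = 0.381, which means a standard deviation of about 39.3 if the difference is 15 units. So 120 is neither confirmed nor refuted, and d = 0.381 is an inference, not a stated design effect.

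**2. Number of primary comparisons.** Abstract: 1. Endpoint section: 3 × 2 = 6. Sample size: two scores, with the deciding time not stated.

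**3. If any one of six sufficed at 5%.**
- Independent tests: 1 − 0.95⁶ = 0.265. For two-sided tests on jointly normal statistics this is the maximum.
- Equal correlation r between all six: 1 − ∫ [Φ((c − √r·u)/√(1−r)) − Φ((−c − √r·u)/√(1−r))]⁶ φ(u) du, with c = 1.96.

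| Assumed r | Chance of at least one false positive |
|---|---|
| 0 | 26.5% |
| 0.5 | about 21% |
| 0.7 | about 16% |
| 0.9 | about 11% |

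A structure in which the correlation between different scores at different times is the product of the two correlations gives slightly more: 22.0%, 17.7% and 11.5% at 0.5, 0.7 and 0.9. All values exceed 5%. The two interim looks are not included.

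**4. If VAS and Calcaneodynia must both succeed.** With 80% power each, joint power is P(Z₁ > −0.842 and Z₂ > −0.842). At r = 0 this is 0.8 × 0.8 = 0.64; at r = 0.8 it is about 0.73.

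**5. If all six stay primary with Bonferroni.** Each test is at 0.05/6 = 0.0083, critical value 2.638. With 108 evaluable per arm and the back-solved effect, power per test is Φ(2.802 − 2.638) = Φ(0.164) ≈ 0.56. Restoring 80% per test takes 108 × ((2.638 + 0.842)/2.802)² ≈ 167 evaluable, or 167/0.9 ≈ 186 per arm.

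**6. If there is one primary comparison.** Its error is 5% before any interim look, and 120 per arm need not change for multiplicity.

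**The case against.** The strongest reply is that this is a condensed article and the analysis plan is not shown. A multiplicity rule may sit there, so its absence here is not a defect. That stands. A reader might infer that the trial may claim success on any of six results, but the document states no such rule; it says only that results will be compared. The 26.5% is therefore what would follow under one possible rule, and it needs independence, which is implausible for related scores measured repeatedly in the same patients. The power figures likewise depend on assumptions labelled above.

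A second reply is that the abstract is shorthand for the body. That does not reconcile them: the abstract has one time point and the body two, and the sample size leaves out a score that the body calls primary. Nor can the 48-week sum scores be read as loosely labelled secondary measures, because the secondary endpoints have their own list.

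Two further inferences go too far. The abstract does not name VAS, so choosing it is a judgement. And a reader might take the 12-week assessment to precede every second radiotherapy series. Therapy protocol offers that series from a minimum of twelve weeks, so the two can coincide.

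**Conclusion.** The finding holds as an internal contradiction. Three sections give three different answers to what is primary, and article length does not explain that. It must be fixed, because the deciding result is undefined.

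The contradiction itself rests on no assumption. Its consequences do:

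- Any-of-six testing would give a family-wise error of roughly 11% to 26.5%, depending on correlation.
- Requiring both powered scores would give about 64% to 73% power, if 80% applies to each.
- Bonferroni over six would leave about 56% per test, given the back-solved effect.

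The document does not show that any of these is the intended rule. What it does show is that no reading with more than one primary comparison has been demonstrated to keep both the 5% and the 80%.

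**What to change.** State the same single primary endpoint in the abstract, the sample-size paragraph and the endpoint section. VAS at 12 weeks is the natural choice: it measures pain, it is named in the sample size and it matches the abstract's time point.

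Make the remaining comparisons secondary and test them in this order, each at 5% and only if the previous one is significant:

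1. Calcaneodynia sum score at 12 weeks
2. SF-12 sum score at 12 weeks
3. VAS at 48 weeks
4. Calcaneodynia sum score at 48 weeks
5. SF-12 sum score at 48 weeks

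State the 80% power for the primary endpoint only, and tie the criterion of significantly different results in Therapy protocol to that endpoint. If the sponsor prefers to keep several primary endpoints, the rule for combining them must be stated and the sample size redone.

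**Cost.** No extra patients are needed for multiplicity. Calcaneodynia, SF-12 and 48-week results can no longer carry the trial on their own, and Calcaneodynia loses its place in the power statement. Since 120 patients are enrolled and the interim analysis is under discussion (Present status of the trial), the change must be a dated amendment made before anyone sees results by arm.

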### Secondary endpoints

SF-12 single scoreCalcaneodynia single scoreEvent-free interval

### Radiotherapy methods

Radiotherapy is performed under orthovoltage conditions (200–250 kV) or high voltage conditions using a cobalt unit or high energy photons of linear accelerators (up to 6 MV without bolus, 10 MV with a bolus of 1 cm).

For orthovoltage therapy, a plantar direct field with tissue equivalent bolus material affixed around the heel is used (‘Essen technique’). The dose should be standardized to a fix reference point (i.e. in 5 mm tissue depth).

For cobalt units or linear accelerators isocentric lateral parallel opposing portals are used (isocenter: center of calcaneus).

The dose is computed either by individual calculation or by depth- dose curves/charts of the therapy machines. The target volume should involve the calcaneus, plantar aponeurosis and the pain point including a safety margin of 2 cm. Gonads have to be shielded as well as possible.

### Quality assurance

Methods to ensure quality are especially:Questionnaires are signed for accuracy by physician and physicistVisiting and personally initiation of all participating centers. Participating centers will additionally been asked to send x-rays, portal imaging pictures and therapy plans of randomly selected patients to the study centerData entered into database will be checked independently by two physicians

### Ethics

The trial protocol has been approved by the Ethics committee of the Saarland Physicians’ Chamber (number 14/07 on 09/05/2012). Furthermore, it has been approved by the board of directors of the DEGRO (German Society for Radiation Oncology).

### Accrual time

Accrual of patients has begun in February, 2013 and is planned to last three years.

### Present status of the trial

In the meantime 120 patients have been enrolled into study. The interim analysis is under discussion. Besides Saarland University Medical School, two further centers are actually enrolling patients.

## Abbreviations

AP-1: Activator protein-1
CCL: Chemocine ligand
cm: Centimeter(s)
DEGRO: German Society for Radiation Oncology
GCGBD: German Cooperative Group for Radiotherapy for Benign Diseases
Gy: Gray
iNOS: Inducible nitric oxide synthetase
kV: Kilovolt
MR: Magnetic resonance
MV: Megavolt
NO: Nitric oxide
pH: Pondus hydrogenii
SF-12: Short Form-12
TGFβ1: Transforming growth factor β1
VAS: Visual analogue scale
